### Harms and adverse events

3.11

Participants’ physical conditions will be closely monitored throughout the trial. Any adverse events (AEs) related to the interventions (e.g., falls, muscle strain) will be recorded and reported in accordance with CONSORT guidelines for non-pharmacological trials. Serious adverse events (SAEs), defined as any unexpected medical occurrence that results in death, is life-threatening, or requires hospitalization, will be specifically documented and handled according to ethical requirements. Before each remote session, participants will receive clear safety instructions and will be asked to report any discomfort immediately through the online platform or by phone. If any participant experiences discomfort during a session, the activity will be immediately halted and medical consultation will be arranged promptly. The research team will follow up as needed and provide appropriate advice, including referral for medical care if necessary. All reported adverse events will be reviewed by a designated safety monitor who is independent of the intervention team.

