#### Dropout criteria

3.2.3

Disease progression during the study period (e.g., advancement to Hoehn & Yahr Stage III).Serious adverse events (e.g., falls resulting in fractures).Inability to continue the intervention for any reason or voluntary withdrawal from the study.

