### Subject grouping

3.3

All participants will receive a comprehensive explanation of the study’s objectives, procedures, potential benefits, and possible risks before the trial. They will voluntarily sign an informed consent form and will be informed that they can withdraw from the study at any stage without any adverse consequences. After completing the informed consent process, participants will be randomly assigned in a 1:1:1 ratio to one of three groups—the Qigong group (QG), the conventional exercise rehabilitation group (EG), or the control group (CG)—using a computer-generated random number table. Participants in both the Baduanjin Qigong and conventional exercise rehabilitation groups will receive three remote live training sessions per week and will be encouraged to perform an additional two to three self-guided sessions weekly. Participants in the control group will maintain their usual daily activities without additional exercise intervention, but will be required to complete regular follow-ups and assessments.

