### Control group (CG)

3.8

Participants in the control group will not receive specific exercise guidance and will be instructed to maintain their usual daily activities. Researchers will conduct regular monthly follow-ups to assess participants’ status and to confirm that they do not engage in additional exercise interventions during the study period.

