### Adherence monitoring

3.10

To ensure participant compliance and maximize the effectiveness of the interventions, all participants in the Qigong group and the conventional exercise rehabilitation group will be required to submit weekly practice logs reporting their training completion, experience, and any discomfort. Participants may submit these practice logs in written form via email, text message, or instant messaging apps, depending on their preference and convenience. Alternatively, participants who find it difficult to submit written logs will have the option to report verbally through a scheduled phone call with a designated member of the research team. For each participant, a designated research member will maintain regular contact. If a participant does not submit their weekly report on time, the research team will proactively follow up by phone or instant messaging apps to remind them to submit their practice log. To further promote accountability and adherence, each participant will receive a minimum of two phone check-ins per month.

During these calls, the research team will:

Review the participant’s training progress and address any questions about the intervention.Provide coaching tips or practical advice to help overcome any difficulties in following the exercise program.Discuss potential barriers to adherence (e.g., time constraints, technical issues) and offer feasible solutions.Encourage participants to continue practicing regularly and highlight the importance of consistent participation for achieving the expected benefits.

These follow-up communications will be documented in the study records. If a participant repeatedly fails to submit practice logs or shows signs of poor adherence, the research team will provide additional personalized guidance and, if necessary, involve family members to support the participant’s continued engagement.

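### Adverse events are recorded only under a rule of relatedness to the interventions, and are sought unequally by arm, so exercise harms cannot be validly compared with control; the two descriptions of a serious event also disagree

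*Protocol article*

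**What the plan says.** **Recording rule.** Section 3.11 (Harms and adverse events) commits to this: "Any adverse events (AEs) related to the interventions (e.g., falls, muscle strain) will be recorded and reported". The article gives no rule for events not considered related. Section 3.8 gives the control group (CG) no exercise programme.

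**Serious events.** Section 3.11 has them "defined as any unexpected medical occurrence that results in death, is life-threatening, or requires hospitalization". Section 3.2.3 (Dropout criteria) gives its own example, "Serious adverse events (e.g., falls resulting in fractures", with no condition on expectedness or admission.

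**How events come to light in the Qigong (QG) and conventional exercise (EG) arms.**
- Section 3.3: both arms "will receive three remote live training sessions per week".
- Section 3.11: "Before each remote session, participants will receive clear safety instructions and will be asked to report any discomfort immediately".
- Section 3.10: both arms "will be required to submit weekly practice logs reporting their training completion, experience, and any discomfort".
- Section 3.10 also says that "each participant will receive a minimum of two phone check-ins per month". The calls deal with training progress, coaching and barriers to adherence.

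**How events come to light in CG.** Section 3.8: "Researchers will conduct regular monthly follow-ups". Their stated purpose is to check status and the absence of extra exercise. No adverse event question is mentioned.

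**Text that helps.** Section 3.11 opens with a general commitment to watch participants' physical condition. It also sends every reported event to a safety monitor independent of the intervention team. All arms are assessed at Weeks 1, 6 and 12.

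**The concern.** Falls are the first example in the recording rule. They also occur in Parkinson's disease without any exercise programme: the Background lists postural instability among the key symptoms, and section 3.15.3.2 uses the Timed Up and Go partly to assess fall risk. Whether remote exercise at home adds falls, prevents them or makes no difference can be read only against falls in the control arm, counted in the same way.

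The rule makes relatedness a condition for an event to enter the data. It should be an attribute assigned after capture. The independent monitor sees what has been reported and cannot recover what was never recorded. Unequal questioning adds a second problem: even with a neutral rule, the arm asked more often will report more.

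The wording on serious events is a separate matter. If two sections classify the same fracture differently, the count of serious events depends on which section the person filling in the form has read.

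**Working it through.** The plan gives no figure to reproduce. The check sets the rules side by side and counts contacts.

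**Step 1. Apply the rules as worded to the same event in different arms.**

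| Event | Related-event rule, 3.11 | Serious under 3.11 | Serious under 3.2.3 |
|---|---|---|---|
| Fall without injury, QG or EG, judged related | recorded | no | no |
| Fall without injury, CG | no rule covers it | no | no |
| Fall with fracture, no admission, not life-threatening, any arm | recorded if judged related | no | yes |
| Fall with fracture, admitted, held to be unexpected, any arm | recorded if judged related | yes | yes |
| Fall with fracture, admitted, held to be foreseeable, any arm | recorded if judged related | no, on a strict reading | yes |

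Row 2 is the gap in control counts. Rows 3 and 5 are where the two sections disagree.

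**Step 2. What the relatedness rule does to the comparison.** If it is applied perfectly, background falls are left out in every arm, and the listing shows only falls attributed to exercise. A reduction in falls could then never appear. If some background falls in QG or EG are attributed to exercise, they are counted there while those in CG are not. The difference from control therefore depends on the attribution, and the recorded data cannot separate the two.

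**Step 3. Count the stated occasions for reporting over 12 weeks.** 12 weeks / 4.345 weeks per month = 2.76 months.

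- Live sessions, QG and EG: 3 × 11 = 33 to 3 × 12 = 36. The lower figure leaves out QG's first week, which section 3.6 describes as instruction.
- Weekly logs, QG and EG: 12.
- Calls, at least two a month: 2 × 2.76 = 5.5, about 6.
- CG follow-ups, monthly: 1 × 2.76 = 2.8, about 3.
- Post-baseline assessments common to all arms: 2 (Weeks 6 and 12).

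Occasions with a stated request about discomfort: 33 + 12 = 45 to 36 + 12 = 48 in QG and EG, and none stated in CG.

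All scheduled contacts, under each reading of the text:

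| Reading | QG or EG | CG | Ratio |
|---|---|---|---|
| Sessions counted, calls to exercise arms only | 53 to 56 | 3 + 2 = 5 | 10.6 to 11.2 |
| Sessions counted, calls to all arms | 53 to 56 | 3 + 6 + 2 = 11 | 4.8 to 5.1 |
| Sessions not counted, calls to exercise arms only | 12 + 6 + 2 = 20 | 5 | 4.0 |
| Sessions not counted, calls to all arms | 20 | 11 | 1.8 |

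The ratio runs from about 2 to about 11. It measures opportunity to report and does not translate directly into event rates.

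**Step 4. Why equal questioning matters even after the rule is mended (illustration, assumed values).** Suppose all events were recorded regardless of relatedness, the true risk were equal in every arm, and an exercise arm captured 95% of affected participants against 50% in CG. With 50 per arm, the recorded numbers would be:

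- true risk 10%: 50 × 0.10 × 0.95 = 4.8 against 50 × 0.10 × 0.50 = 2.5
- true risk 20%: 9.5 against 5.0
- true risk 30%: 14.2 against 7.5

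With 80% capture in the exercise arm, the first figures become 4.0, 8.0 and 12.0. Risks and capture rates are assumptions; the documents give none.

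**The case against.** Several points on the other side have force.

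- **The article does not say that unrelated events are discarded.** True. But it states a rule for related events and none for the rest, and the general commitment to watch participants supplies no recording rule.
- **A reader might infer that CG will show no events of any kind.** The text does not support that. The sentence on serious events has no relatedness or arm condition, so an unexpected admission in CG would be documented. The gap is mainly in non-serious events.
- **A reader might infer a large false excess of falls in QG.** That would require background falls in QG to be misjudged as related. Applied correctly, the rule would exclude them there too.
- **A reader might infer that relatedness is judged by unblinded staff, or that the protocol classes falls as expected.** Neither is stated. The article does not say who judges relatedness or whether the safety monitor is blinded. Falls are given as examples of related events, and there is no list of expected events. The word unexpected may mean no more than unplanned, so the loophole for admitted falls rests on a strict reading.
- **A reader might infer that serious falls go unreported in general.** In QG and EG a related fall is still recorded as an adverse event, a fracture is a dropout criterion, and participants who withdraw are asked why.
- **The calls may reach all arms.** The wording about each participant is ambiguous, although the content of the calls concerns training. Step 3 shows both readings.
- **Closer monitoring of people exercising at home is a safety measure.** Agreed; it should stay.
- **Harms are not a listed outcome, and the full protocol may hold the forms and questions.** This limits the weight of the point. The recording rule and the two accounts of a serious event are nevertheless stated in the article, so they are not details left to another document.

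**Conclusion.** The point stands in a limited form. Followed as worded, the plan yields no usable control-arm count of non-serious adverse events or falls, and it seeks events more intensively in the exercise arms. Harms in QG or EG therefore cannot be validly compared with CG, in either direction. The size of the distortion cannot be given, because it depends on how relatedness is attributed and on capture rates that the documents do not state. What can be counted is opportunity: 45 to 48 stated requests about discomfort against none stated in CG, or about 2 to 11 times as many scheduled contacts, depending on the reading.

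The comparison of QG with EG is little affected, since both have the same logs and the same session frequency. No efficacy conclusion changes.

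Separately, sections 3.2.3 and 3.11 disagree on what makes a fall with fracture a serious event. On a strict reading, a fracture without admission, or an admitted fall held to be foreseeable, could fall outside the definition in section 3.11. The change should be made, but the trial's main conclusions do not depend on it.

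**What to change.** 1. In section 3.11, record all adverse events and all falls in all three arms regardless of relatedness. Assess relatedness and expectedness afterwards, as attributes of each recorded event.
2. Ask every arm the same short question on adverse events and falls at common times: the monthly contact, Week 6 and Week 12. Base any comparison between arms on those reports.
3. Keep the session prompts and weekly logs in QG and EG as safety monitoring, and report what they yield separately.
4. State whether the calls in section 3.10 include CG.
5. Separate seriousness from expectedness in the definition of a serious event, and reconcile it with the fracture example in section 3.2.3.

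The cost is protocol wording, one short question at contacts already planned, and slightly more adverse event paperwork. No extra visit is needed.

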### Participant timeline

3.12

Figure 2 offers a comprehensive timeline of participant enrollment, intervention implementation, and assessment points across the study period. Assessments will be conducted at baseline (Week 1), interim (Week 6), and final (Week 12).

**Figure 2 fig2:**
[figure not shown]
SPIRIT schedule of entrollment, interventions, and assessments.

### Outcomes

3.13

All outcomes will be measured and documented at baseline assessment (Week 1), interim assessment (Week 6), and final assessment (Week 12). The primary outcomes are quality of life, assessed using the Parkinson’s Disease Questionnaire-39 (PDQ-39), the MOS 36-item Short Form Health Survey (SF-36), and the Unified Parkinson’s Disease Rating Scale developed by the Movement Disorder Society Part I (MDS-UPDRS Part I). The second indicator is physical function, which covers Reaction time, Balance, Physical coordination, Flexibility, and Walking capacity.

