#### PDQ-39

3.14.1

PDQ-39 (24, 25) is a validated questionnaire specifically designed to assess quality of life in PD patients. It has demonstrated high reliability and validity and is widely applied in PD-related research. The PDQ-39 encompasses eight domains: mobility, activities of daily living (ADL), emotional well-being, stigma, social support, cognitive impairment, communication, and bodily discomfort.

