#### MDS-UPDRS part I

3.14.3

MDS-UPDRS represents one of the most widely used tools to assess PD progression (27). MDS-UPDRS Part I will be used in this study to assess non-motor experiences of daily living in individuals with PD. Part I consists of patient-reported items evaluating symptoms such as cognitive impairment, mood disturbances (e.g., depression, anxiety), sleep problems, pain, urinary issues, and fatigue. Higher scores indicate greater severity of non-motor symptoms. MDS-UPDRS Part I has demonstrated high internal consistency (Cronbach’s *α* = 0.85), small floor and ceiling effects (2 and 0%, respectively), and good concurrent validity (correlation with the original UPDRS Part I: r = 0.81, *p* < 0.001) (28). Its inclusion in this study will provide a comprehensive evaluation of the non-motor aspects of patient well-being, complementing the broader quality of life assessments captured by the PDQ-39 and SF-36.

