### Statistical analysis

3.17

A mixed-effect model will be employed to analyze the experimental data, accounting for individual variability. The model will assess the random effect of participants while adjusting for baseline variables. Baseline characteristics will be compared between groups using appropriate statistical tests (e.g., one-way ANOVA for continuous variables, chi-square test for categorical variables) to ensure group equivalence prior to intervention. If any significant baseline differences are found, they will be adjusted for in the subsequent analyses. To account for differences in exercise intensity and total dose between groups, weekly exercise volume (MET-hours/week) will be calculated and included as a covariate in the mixed-effect model. Intergroup comparisons will be conducted without multiple comparison adjustments. The differences in intervention effects among the three groups will be calculated and expressed as effect sizes with 95% confidence intervals (CIs). For outcome analyses, mixed-effect models will be primarily employed to analyze repeated measures across time points. When analyzing between-group differences at individual time points, one-way ANOVA or Kruskal-Wallis test will be applied, depending on data distribution and normality assumptions. Pairwise post-hoc comparisons will apply Bonferroni correction. All statistical analyses will be conducted using SPSS 26.0 and R 4.0.2, with a significance level of *p* < 0.05.

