### Sample size

3.19

The sample size estimation was based on expected changes in PDQ-39 total score, assuming a minimum clinically significant difference of 5 points between groups. Using a power of 80% (1-*β* = 0.80) and a significance level of 0.05 (two-tailed), the required sample size was calculated using G*Power 3.1. Given an estimated standard deviation (SD) of 10.5 and an effect size of 0.5, the initial calculation suggested 42 participants per group. Considering a potential 15% dropout rate, the final sample size was increased to 50 participants per group, resulting in a total of 150 participants.

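### MDS-UPDRS Part I is listed as one of three unranked primary measures of quality of life, but the protocol describes it as a non-motor symptom-severity score that complements the quality-of-life scales

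*Protocol article*

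**What the plan says.** The Abstract (Methods/design) and section 3.13 (Outcomes) give one primary construct, quality of life, and three instruments for it. Section 3.13 reads "The primary outcomes are quality of life, assessed using the Parkinson’s Disease Questionnaire-39 (PDQ-39", then adds SF-36 and "the Unified Parkinson’s Disease Rating Scale developed by the Movement Disorder Society Part I (MDS-UPDRS Part I". Section 3.14, headed as quality of life, holds a subsection for each of the three.

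The subsections describe them differently. PDQ-39 is (3.14.1) "a validated questionnaire specifically designed to assess quality of life in PD patients". For Part I (3.14.3) the protocol says "MDS-UPDRS Part I will be used in this study to assess non-motor experiences of daily living in individuals with PD" and "Higher scores indicate greater severity of non-motor symptoms". The same subsection closes by saying that Part I covers non-motor aspects of well-being, "complementing the broader quality of life assessments captured by the PDQ-39 and SF-36".

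Section 3.19 sizes the trial on one scale: "The sample size estimation was based on expected changes in PDQ-39 total score". Section 3.17 says "Intergroup comparisons will be conducted without multiple comparison adjustments" and, later, that post-hoc pairwise comparisons get a Bonferroni correction. Neither sentence orders the three primary scales or says how many must show an effect.

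**The concern.** The primary conclusion will be worded as quality of life. Section 3.14.3 attributes the quality-of-life assessment to PDQ-39 and SF-36 and sets Part I beside them as a symptom score, yet section 3.13 gives Part I equal standing as a measure of the endpoint.

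This matters because the scales could diverge. The Background expects Baduanjin to help with anxiety, depression and sleep, and section 3.14.3 lists mood and sleep problems among the Part I items. If Part I improved while PDQ-39 and SF-36 did not, nothing in the protocol would stop the result from being presented as a primary quality-of-life benefit. A reader of the trial report would take that as a statement about the broader construct.

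**Working it through.** The point turns on the text, so the main check is to set the statements side by side.

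1. **Assigned role.** Abstract, 3.13 and 3.14: Part I is a primary quality-of-life measure, equal in rank to PDQ-39 and SF-36.
2. **Described content.** 3.14.3: non-motor experiences of daily living, with the score read as symptom severity.
3. **Described relation.** 3.14.3: Part I complements the broader quality-of-life assessments, which are credited to the other two scales.
4. **Supporting evidence.** The validity evidence cited for Part I is internal consistency (Cronbach's α = 0.85), floor and ceiling effects (2% and 0%), and correlation with the original UPDRS Part I (r = 0.81). These describe Part I as a scale of its own kind. None relates it to a quality-of-life measure. PDQ-39, by contrast, is described as built for quality of life.
5. **Links the other way.** The Background describes the decline in quality of life partly through sleep and emotional symptoms, and says that Baduanjin raises quality of life by relieving anxiety, depression and poor sleep. Content overlaps too: PDQ-39 has emotional, cognitive and bodily-discomfort domains, SF-36 has pain, vitality and mental health, and Part I has cognition, mood, pain and fatigue.
6. **Success rule.** None is stated. The Bonferroni sentence in 3.17 concerns pairwise comparisons of groups; it is not said to cover the three scales.

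Items 1 to 3 do not sit together. Item 5 limits the conclusion to a narrower, related measure. Item 6 is what lets the mismatch reach the primary conclusion.

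**What can be counted.** Part I is one of three primary instruments. The labelling has no error rate. For scale only, assume a rule that the protocol does not state: each scale is tested at 0.05 and any one suffices. For one group contrast with no true effects and independent scales:

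- three scales: 1 − 0.95³ = 14.3% chance of at least one false positive;
- PDQ-39 and SF-36 only: 1 − 0.95² = 9.75%;
- Part I alone positive: 0.05 × 0.95² = 4.5%.

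With an assumed pairwise correlation of 0.5 to 0.7, simulation puts the last figure at about 3.5% to 2.6%. These are chance findings under an assumed rule. They do not measure how often a real Part I effect would be given the wrong name.

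**Sample size.** The only figure used here is the choice of PDQ-39 as its basis. The stated 42 per group does not reproduce at two-sided 0.05 and 80% power. By normal approximation, 5/10.5 = 0.476 needs 70 per group and an effect size of 0.5 needs 63. The dropout step does reproduce: 42/0.85 = 49.4, rounded up to 50. The shortfall is a separate matter, and this point does not depend on it.

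**The case against.** The strongest reply is that the protocol treats non-motor symptoms as part of quality of life. The Background does so twice, and the word broader in 3.14.3 can be read as placing Part I as the narrower member of one family. No sentence says that Part I does not measure quality of life. This stands. A reader might infer from 3.14.3 that the protocol declares Part I to be a measure of something else altogether; the documents do not support that reading.

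A reader might also infer that the plan endorses a primary claim on Part I alone. It does not: it states no success rule. A rule giving PDQ-39 precedence, or one requiring all three scales to succeed, would remove the risk, so it would be wrong to say that the problem survives any multiplicity rule. An analysis plan that is not shown may contain such a rule. This also stands, and it makes the risk possible rather than certain.

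Two further arguments carry no weight for the point. That only PDQ-39 enters the sample size says nothing about construct, since the same is true of SF-36. A power figure for Part I would not measure the problem either: it would be ordinary power for a real effect, and the effect size of 0.5 in 3.19 is given for PDQ-39 only.

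The reply does not remove the mismatch. Overlap in content does not turn a symptom-severity score into a quality-of-life score of equal standing, and 3.14.3 itself keeps the two apart. Even if an unseen plan ranked the scales, the Abstract and 3.13 would still present them as equals.

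**Conclusion.** The point holds in a limited form. The protocol gives Part I equal standing as a primary quality-of-life measure in one place, and in another describes it as a symptom-severity score that complements the quality-of-life scales. With three unranked scales and no success rule, a Part I result alone could carry the primary quality-of-life conclusion.

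The extent is one of three primary instruments. Whether harm follows depends on two things not known from the document: whether Part I diverges from the other two scales, and whether a ranking exists elsewhere. The conclusion rests on the protocol's own descriptions and on no outside view of what the scale measures.

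**What to change.** Name PDQ-39 total score as the primary quality-of-life outcome and SF-36 as supporting. Report MDS-UPDRS Part I as a secondary outcome under its own heading, non-motor symptoms. State that the quality-of-life conclusion rests on PDQ-39.

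This means editing the Abstract and sections 3.13, 3.14 and 3.14.3 so that they agree, checking the registry entry (not seen here) for the same wording, and dating the change before outcome data are examined by group. The data collected do not change. The cost is fewer primary outcomes on which to claim success.

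If the sponsor prefers to keep Part I primary, the lesser alternative is to rename the primary construct so that it covers non-motor symptoms and to state how the three scales are ranked or combined. That settles the wording, but a separate sentence would still be needed on which scale supports a claim about quality of life.
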